#### Diet and weight loss

All participants are encouraged to achieve three overarching dietary aims: 1) increasing intake of vegetables, fruit and whole grains; 2) reducing intake of foods high in added sugars and fat (especially saturated fats) and 3) limiting portion size and improving dietary quality. In addition, those who are overweight and want to work towards modest weight loss (i.e., 5–10 % of initial body weight) focus on reducing energy intake by 2,000 kJ per day. Strategies to reduce energy intake include: improving portion control (by reducing portion size or number of serves) and lowering energy density (by increasing intake of low energy dense foods such as fruits and vegetables and reducing intake of foods with high energy density such as high fat/sugar foods).

### Data collection

All study data are collected by study-trained Cancer Council staff as this enables capacity building for ongoing program evaluation. Study funding is used to ensure that each Cancer Council has a dedicated research assistant to support evaluation. Study protocol implementation and data quality control are monitored via weekly database reports submitted by Cancer Council staff to the research team.

### Primary and secondary outcomes

Outcomes are shown in Table 5, along with the relevant RE-AIM indicators and measurement tools. Primary (service-level) outcomes include referrals, call delivery, completion rates, participant and staff satisfaction and program delivery costs, and will be systematically collected in each of the Cancer Council databases. Secondary (anthropometric, behavioural and psychosocial) outcomes are patient-reported during pre- and post-program assessments conducted by Cancer Council staff via telephone and using validated protocols and questionnaires.

**Table 5 Tab5:** Primary and secondary outcomes, assessment tools and RE-AIM indicators

Setting	RE-AIM indicator	Collection method/assessment tools
Primary Outcomes		
Referring Sites	Adoption & Maintenance	
	Type of referring site and # of referrals	CC database
	Staff satisfaction and feedback on sustainability of referral protocol	Interview
Cancer Councils	Reach & Representativeness	
	% uptake among eligible survivors	CC database
	Participant characteristics	CC database
	Implementation	
	Participant consent rates	CC database
	Completion rates	CC database
	Withdrawal rates and reasons	CC database
	Number of intervention calls	CC database
	Length of intervention calls	CC database
	Administration time for intervention calls	CC database
	Intervention content covered	CC database
	Completion of pre- and post-program assessments	CC database
	Adverse events	CC database
	Healthy Living after Cancer nurse/allied health professional and CC manager satisfaction	Interview
	Economic Appraisal	
	Costs to deliver the Healthy Living after Cancer program	Documentation of resources utilised for Healthy Living after Cancer service delivery
Secondary Outcomes		
Consumer	Effectiveness	
	Anthropometric Outcomes	
	Weight, height, waist circumference	Self-reported
	Behavioural Outcomes	
	Physical Activity	Active Australia Survey [83]
	Sedentary Behaviour	Single item from the International Physical Activity Questionnaire (short, last 7 days format) [84]
	Diet	Fat and Fibre Behaviour Questionnaire [85]
		Daily servings of fruits and vegetables [86]
	Psychosocial Outcomes	
	Quality of Life	Short-Form Health Survey (SF-12), v1.0 [87]
	Cancer and treatment-related symptoms and side-effects	MD Anderson Symptom Inventory [88]
	Fear of Cancer Recurrence	The Concerns about Recurrence Questionnaire – 4-item (CARQ-4) [89]
	Distress	2-item Distress Thermometer assessing distress (adapted from the National Comprehensive Cancer Network Distress Thermometer for Patients) [90] and impact of distress [91]
	Healthy Living after Cancer program satisfaction	Self-reported (rating scales and comments)

*CC* Cancer Council

### Statistical analyses

Primary outcomes for HLaC implementation will be reported descriptively. Analyses of secondary (effectiveness) outcomes will be by mixed models, which allow for repeated measures (baseline and follow-up) and will include all participants with baseline data (including those with missing data at follow-up) with adjustment for predictors of dropouts to minimise non-response bias. Data will be analysed collectively (pooled) across Cancer Councils as well as reported individually for each. To minimise type I errors because of testing multiple outcomes, significance will be set at *p* < 0.001 (two-tailed). Sensitivity of conclusions to missing data assumptions will be evaluated.

### Sample size related to secondary (effectiveness) outcomes

Given the resources available in each Cancer Council to support HLaC implementation, the service delivery is expected to provide a sample size of approximately 900 participants across the four participating Cancer Councils over the three year recruitment period. This sample provides >90 % power with two-tailed significance of *p* < 0.001 to detect pre-post changes of 60 minutes of physical activity per week, 0.5 serves of fruit or vegetables, 2 kg weight and clinically relevant changes in physical and mental components of quality of life (3 units each) [71], based on assumed standard deviations of change of 300 min/week, 1.5 fruit and 2 vegetable serves, 8 kg weight, and 8 units on the mental and physical component scores. These calculations allow for 30 % participant attrition and adjustment for up to 10 covariates (10 observations per covariate).

### Economic appraisal

The economic questions associated with this research relate to the costs of implementing HLaC and the relationship between costs, program completion and outcomes. Specifically:*Costs of implementing HLaC:* The fixed costs (i.e., expenditure required to deliver the HLaC program, including resources associated with modifying Cancer Council databases, refining referral pathways, adapting the intervention and evaluation protocols and recruiting and training nurses) will be documented. Dollar values will be attached to these resources using publicly available information such as appropriate salary rates for the time of personnel involved in the above activities and commercial prices for the production of any training materials, etc. Fixed costs will be allocated equally over all participants who consent to participate in HLaC. Variable costs (i.e., those that are proportional to the volume of service provided) will be allocated in proportion to the stage of HLaC reached by individuals [72].*Relationship between costs, completion and outcomes:* Stage of completion will be defined as follows: Stage 1 = completion of ≥3 x weekly phone calls; Stage 2 = completion of Stage 1 + ≥3 x fortnightly phone calls; Stage 3 = completion of stages 1 + 2 + ≥3 monthly calls. For the purposes of the economic appraisal, outcomes will be defined using a series of pre-defined benchmarks based on pre-post program changes in the behavioural and anthropometric variables. For total physical activity, participants who reported achieving 150 minutes/week are considered as having made improvements in their physical activity level. For vegetables and fruit, participants who reported achieving the target of 5 and 2 serves/day, respectively, are classified as having made positive changes in their dietary behaviour. For weight (among participants where weight loss is indicated), those who recorded a body weight reduction at follow-up ≥3 % of their baseline weight will be classified as having successfully achieved a health enhancing benefit [73]. Regression analysis will be used to assess the relationship between completion of stages and outcomes achieved. It is hypothesised that those who complete Stage 3 will have better outcomes than Stage 2 completers who in turn will have better outcomes than those who do not proceed beyond Stage 1. Pre- and post-test differences will be calculated as changes in Quality of Life (SF-12) and Quality Adjusted Life Years (QALYs) SF6D [74] (calculated from SF-12). Data will be analysed with and without imputed outcomes. Sensitivity analysis will be used to explore the impact of varying assumptions about the cut-offs used to define improvements in the secondary outcomes noted above.

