The five-year study will be conducted in three phases: Phase 1 involves knowledge transfer and capacity building (Year 1). In this phase, the research team will work closely with Cancer Council partners to facilitate their ability to implement and evaluate HLaC, including database adaptations, staff training and input from Cancer Council staff on program materials. Phase 2 involves HLaC implementation and evaluation (Years 2–5), with intervention procedures and the evaluation plan described below. Phase 3 involves advocacy within the Cancer Councils, alongside communication of HLaC outcomes to the broader cancer control community and health care sector, in an effort to obtain sustained funding for the program (Years 4–5).

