### Accrual targets

The overarching aim is for each Cancer Council to deliver the program over a three-year period. This should afford adequate experience with program implementation and familiarity with outcomes to inform decisions on program sustainability. Accrual targets for each Cancer Council are based on available resources to implement the program. There is capacity for each participating Cancer Council to achieve approximately 50–60 program completions/year implementing the HLaC program 6-month/12 call protocol (refer to the program delivery section). With an estimated 30 % attrition, each Cancer Council would therefore need to enrol approximately 75–80 participants per year. The attrition estimate is based on the high (nearly 50 %) attrition observed in other disseminated lifestyle intervention programs in the general adult population [58, 59], but tempered by the fact that cancer survivors tend to be highly motivated such that cancer-specific trials generally achieve 90 % 12-month retention [32, 35, 52, 53, 60]. Across the three years of HLaC implementation, it is anticipated that each Cancer Council will achieve completion rates of approximately 150–180 participants, for a total of approximately 600–680 HLaC completing (from 900 enrolled) during the proposed study (refer to the sample size section).

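### The fixed-cost rule mixes one-off set-up with recurring items, so no planned figure gives the cost of continued delivery

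*Protocol article*

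**What the plan says.** Table 5 (Primary and secondary outcomes) lists "Costs to deliver the Healthy Living after Cancer program" among the primary outcomes. The Economic appraisal section describes the fixed costs as "expenditure required to deliver the HLaC program, including resources associated with modifying Cancer Council databases, refining referral pathways, adapting the intervention and evaluation protocols", and adds the recruitment and training of nurses. The rule for this pool is "Fixed costs will be allocated equally over all participants who consent to participate in HLaC". Variable costs are handled separately and "will be allocated in proportion to the stage of HLaC reached by individuals". The only economic sensitivity analysis named concerns the cut-offs that define improvement. The cost horizon and the content of the cost pool are not varied.

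On timing, the section on the Healthy Living after Cancer partnership places database adaptations and staff training in Phase 1 (Year 1), implementation in Years 2–5, and the effort to secure sustained funding in Years 4–5. On use, the Accrual targets section says: "The overarching aim is for each Cancer Council to deliver the program over a three-year period". It expects that this period will give enough experience and "familiarity with outcomes to inform decisions on program sustainability". The Discussion repeats that the data are meant to inform a decision on sustained funding.

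**The concern.** Two different questions can be asked of the cost data. One is what it took to put the program in place and run it for the study period. The other is what it would take to keep running it. Much of the listed fixed-cost work will already have been paid for when the second question is decided. The stated rule neither separates that work from fixed items that recur nor spreads it over any period longer than the study.

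A Cancer Council or funder deciding on continuation needs the recurring cost per participant and per completer. If the only per-participant totals available carry the study's set-up work, the reader of the cost results has to guess how much of the figure would disappear after the study.

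**Working it through.** **Inputs from the protocol article**
- Four Cancer Councils, three years of delivery, 75–80 enrolments per Council per year (Accrual targets).
- About 900 participants in total (Sample size related to secondary outcomes). I take those enrolled as those who consent.
- New staff may be trained by a lead nurse during the study period (Healthy Living after Cancer program).
- No dollar amounts are given anywhere.

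**The denominator**
- 4 × 3 × 75 = 900, which reproduces the stated total. The upper end is 4 × 3 × 80 = 960.
- At the lower end, yearly throughput is 4 × 75 = 300.

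**What each planned figure contains**

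Let S be the one-off part of the fixed pool, R the part that recurs, N the number consenting and v the mean variable cost per participant. Assume that continued delivery has the same throughput and the same recurring needs.
- Full cost under the rule: (S + R)/N + v
- Cost of continued delivery: R/N + v
- Variable cost alone: v

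The full cost is therefore too high for the continuation question by S/N, and the variable cost alone is too low by R/N. S is not zero, because database modification and protocol adaptation are set-up work. R is not zero if replacement staff have to be recruited and trained. That training does not scale with the volume of service, so under the article's own definitions it belongs with the fixed costs. The list does not say whether its training item covers the initial round only or later rounds too.

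**How S/N moves with study length and accrual** (S = AUD 100,000, assumed only to show the structure)
- N = 900: 100,000/900 = AUD 111
- N = 960: 100,000/960 = AUD 104
- 5 years at 300 a year, N = 1,500: AUD 67
- 6 years, N = 1,800: AUD 56
- 10 years, N = 3,000: AUD 33
- Delivery after set-up has been paid: AUD 0

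The service is the same in every line. Only the number of participants carrying the set-up cost differs.

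**In relative terms**

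If one-off items make up a share s of the full per-participant cost, the full cost exceeds the continuing cost by 1/(1 − s) − 1:
- s = 10%: 11%
- s = 20%: 25%
- s = 30%: 43%
- s = 40%: 67%
- s = 50%: 100%

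The documents do not show where in this range the program lies, or whether it lies in it at all.

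**The case against.** The strongest reply is that the article asks about the cost of implementing the program, and start-up cost belongs in that answer. Five Councils were approached and four joined, so a later adopter would need to know it. The article nowhere says that fixed plus variable cost per participant is the cost of continuing, and it prescribes no single headline figure. Fixed resources are to be documented item by item and variable costs are kept apart, so most of the data for a split will exist. A condensed article may also leave cost categories and horizons to a fuller economic plan.

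Much of this stands. Including set-up is not an error, and the absence of a horizon would not be a finding by itself. What remains is that the article does fix a rule for the whole pool, names continuation as a use of the results, and plans no component that equals continuing cost.

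A reader might also infer three stronger points that the text does not support:
- *That slow accrual would make one Council look expensive.* This requires fixed costs to be divided within each Council. Read literally, the rule pools them, and every participant carries the same charge. Individual reporting by Council is mentioned under Statistical analyses, but the Economic appraisal section does not say that costs are divided that way.
- *That the comparison of costs, completion and outcomes is distorted.* The regression described relates completion stage to outcomes and has no cost term. An equal charge per participant leaves absolute cost differences between stages unchanged.
- *That all evaluation cost should come out of delivery cost.* The Data collection section has Council staff collect the data partly to build capacity for evaluation that continues, so some of it is a service cost.

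**Conclusion.** The point holds as a cheap improvement to a primary outcome. The stated rule suits the cost of implementation. It does not produce the cost of continued delivery: the full per-participant figure lies above that cost by S/N, and variable cost alone lies below it by R/N.

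The direction follows from the contents of the pool, provided that some listed items are truly one-off and some recur. The size cannot be determined. The AUD 100,000 and the shares of 10–50% are assumptions that show how the figure behaves, and they do not support any dollar estimate of overstatement for this program. The power calculation and the effectiveness analyses are unaffected.

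**What to change.** Code each entry in the planned resource documentation as one of three kinds:
1. start-up;
2. recurrent delivery, fixed and variable, including ongoing training and any evaluation that continues as part of the service;
3. research-only.

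Report recurrent cost per participant and per completer alongside the full cost including start-up. Show start-up as a separate sum for each Council, and in sensitivity analysis spread it over stated alternative horizons. Keep only the research-only evaluation out of delivery cost.

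No new data stream is needed. The cost is a coding column and one extra table, and the results no longer reduce to a single headline figure.

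### Variable costs are allocated by stage reached, which follows calls delivered only coarsely and gives no weight to participants with fewer than three weekly calls

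*Protocol article*

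**What the plan says.** The Economic appraisal section of the protocol article treats the two kinds of cost differently. Fixed costs are shared equally among everyone who consents. Variable costs are described as "those that are proportional to the volume of service provided", and the same sentence says that they "will be allocated in proportion to the stage of HLaC reached by individuals".

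The stages are defined just after this, under the sub-heading on costs, completion and outcomes, and each is nested in the one before. The lowest is given as "Stage 1 = completion of ≥3 x weekly phone calls". The second level requires the first and, on top of it, three or more of the fortnightly calls. The third requires both lower levels and three or more of the calls made monthly.

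No stage or cost weight is given for a participant with 0, 1 or 2 weekly calls.

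Table 5 (Primary and secondary outcomes) lists the cost of delivering the program as a primary outcome, measured by documenting the resources used. It also lists the number of intervention calls, "Length of intervention calls" and "Administration time for intervention calls", all held in the Cancer Council databases.

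**The concern.** The definition and the allocation rule in one sentence do not match. If a cost varies with volume, the natural allocation key is volume, and the study records it. A three-level threshold variable discards most of that information and leaves the earliest dropouts without a key.

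The section sets out to relate costs to completion and outcomes. With fixed cost equal for everyone and variable cost set by stage, individual cost depends on stage and nothing else. A cost gradient across stages would then come from the rule and would not be measured. The planned sensitivity analysis varies the cut-offs that define improvement, not the cost allocation, so it would not reveal this. The results are meant to support decisions on continued funding, where cost by level of completion is a figure that people will use.

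**Working it through.** **Inputs**

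- Calls by phase: weekly calls 1-4, fortnightly calls 5-8, monthly calls 9-12 (Table 4, Intervention procedures).
- Maximum of 12 calls (Healthy Living after Cancer program section).
- Stage thresholds: at least 3 calls in each phase, nested (Economic appraisal).
- 900 enrolled and 30 % attrition (Accrual targets).

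**1. The plan's own figure.** 4 + 4 + 4 = 12, which agrees with the stated maximum.

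**2. Sequential dropout.** A participant takes calls in order and stops after call n. Stage 1 is reached at n = 3, Stage 2 at n = 4 + 3 = 7 and Stage 3 at n = 8 + 3 = 11.

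| Stage | Calls delivered | Highest / lowest |
|---|---|---|
| None | 0-2 | not defined |
| 1 | 3-6 | 6/3 = 2.0 |
| 2 | 7-10 | 10/7 = 1.4 |
| 3 | 11-12 | 12/11 = 1.1 |

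The bands do not overlap and they rise with volume, so stage is an ordered but coarse proxy.

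**3. Any attendance pattern.** With 0 to 4 calls in each phase there are 5 × 5 × 5 = 125 patterns.

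| Stage | Patterns | Calls delivered | Pattern with most calls (weekly, fortnightly, monthly) |
|---|---|---|---|
| None | 75 | 0-10 | 2, 4, 4 |
| 1 | 30 | 3-10 | 4, 2, 4 |
| 2 | 12 | 6-10 | 4, 4, 2 |
| 3 | 8 | 9-12 | 4, 4, 4 |

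Ten calls can therefore fall in all four groups. The pattern counts show what is possible, not how often it happens.

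**4. Effect on individual cost.** The document gives no stage weights, so this step rests on an assumption. Suppose weights of 1:2:3, with Stage 3 equal to 12 calls. Stage 1 is then costed at 4 calls and Stage 2 at 8. Under sequential dropout:

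- 3 calls costed as 4: 4/3 − 1 = +33 %
- 6 calls costed as 4: 4/6 − 1 = −33 %
- 7 calls costed as 8: 8/7 − 1 = +14 %
- 10 calls costed as 8: 8/10 − 1 = −20 %
- 11 calls costed as 12: 12/11 − 1 = +9 %

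Other weights move the error but do not remove it. If Stage 1 is costed at 3 calls, a 6-call participant carries 3/6 = 50 % of actual volume. If it is costed at 6, a 3-call participant carries 6/3 = 200 %.

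On actual volume, one or two calls would be 1/12 = 8 % or 2/12 = 17 % of a full course. The rule states no share for them.

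**5. Participants affected.** 900 × 0.30 = 270 is the total expected attrition. The document does not divide it by call number, so the number below Stage 1, and the number misallocated, cannot be derived.

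**The case against.** The strongest reply is that stage reached, in the costing sentence, need not mean the completion stages. Those are defined afterwards, under another sub-heading and a slightly different name. The authors may have meant the delivery phase reached, as in Table 4. On that reading a participant with one or two weekly calls is in phase one and is costed. The text does not settle which is meant. This part of the objection stands, and it rules out saying that the plan costs anyone at zero.

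The phase reading does not rescue the rule, however. Under sequential dropout, phase one would cover 1 to 4 calls, phase two 5 to 8 and phase three 9 to 12. A participant with one call would carry the same variable cost as one with four.

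Three stronger inferences are tempting, and the documents do not support them.

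- A reader might infer that up to 10 delivered calls are costed at nothing. That needs a participant who misses two of the first four weekly calls and then completes all eight later ones, plus a zero weight that the document does not state. Ordinary dropout leaves at most 2 calls without a stage.
- A reader might infer that about 270 participants are affected. That figure is all expected attrition, and many of those participants may reach Stage 1 or 2.
- A reader might infer that the primary cost outcome is wrong. Table 5 obtains it by documenting resources, and allocation only divides a documented total.

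It would also go too far to say that the outcome comparison has no place for people below Stage 1. Its lowest group is those who go no further than Stage 1, and that wording may include them. It is ambiguous.

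**Conclusion.** The point holds in a limited form. The stated rule does not match the plan's own definition of variable cost. It follows calls delivered only coarsely and leaves participants with fewer than three weekly calls without a weight.

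Under sequential dropout, participants in the same stage can differ by a factor of up to 2 in calls delivered (3 against 6), whatever weights are used. With the assumed 1:2:3 weights, individual errors within Stages 1 to 3 run from −33 % to +33 %.

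Total documented cost is unaffected, provided that the documented total is what gets distributed. What changes is its division between individuals and stages, and with it any statement that links cost to completion or to outcomes. The regression of outcome on stage does not use the allocated cost; for that regression, the only open question is where participants below Stage 1 belong.

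The aggregate effect cannot be computed. Because the total is safe and the rule can be changed at analysis, this is a correction worth making but less than essential.

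**What to change.** Replace allocation by stage with costing from recorded use. For each consenting participant:

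variable delivery cost = (total minutes of intervention calls + administration minutes for those calls) × salary rate

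The number, length and administration time of calls are already listed in Table 5, and the Economic appraisal section already plans to use salary rates. Summarise the resulting costs by stage afterwards, so that the cost-completion relationship is measured.

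Add an explicit category for participants below Stage 1 (fewer than three weekly calls), and say whether it is separate from Stage 1 or pooled with it in the outcome comparison. Every consenting participant then has a class.

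Table 5 does not list screening and assessment time as a field. Include it only if it is already documented, or as a standard unit cost per screening or assessment.

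The call-based part needs no new data collection. The price is slightly more analysis work.

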## Background

### Cancer survivorship in Australia

Five-year survival rates for the majority of cancers have steadily improved in Australia over the past decades, from 47 % to 66 % between the periods 1982–1987 and 2006–2010, with rates for the most prevalent cancers - prostate, breast and colorectal cancers - now being 92 %, 89 % and 66 %, respectively [1, 2]. These improvements in survival are also mirrored across other developed countries [3]. However, cancer survivorship brings with it increased risk of cancer recurrence, second primaries, persistent side-effects of treatment, functional decline and co-morbid chronic conditions, such as cardiovascular disease and type 2 diabetes [4–7]. To mitigate these risks and improve the longer-term well-being of cancer survivors, national cancer organisations recommend that cancer survivors engage in regular physical activity, eat a healthy diet and keep their weight within a healthy range [8–10]. Yet, the majority of cancer survivors do not meet these lifestyle recommendations; over 50 % are overweight or obese, over 50 % do not meet physical activity recommendations, and 90 % do not meet dietary guidelines [11–13]. Further, declines in activity and weight gain are common post-cancer treatment [14–16]. Despite a strong desire on the part of most cancer survivors for advice and support regarding healthy lifestyles [17], such assistance is not routinely offered as part of survivorship care [17–19].

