### Healthy Living after Cancer program

The six-month HLaC program is aimed at increasing physical activity, promoting healthy eating, and assisting with moderate weight loss (if indicated), consistent with current evidence and guidelines for nutrition and physical activity in cancer survivors (Table 2) [8–10]. Delivered by study-trained, Cancer Council nurses/allied health professionals with expertise in cancer care, it will provide the necessary support and advice to meet these guidelines while dealing with common cancer survivorship issues including lymphoedema, pain, fatigue and fear of recurrence. Participants will receive up to 12 telephone calls over the 6-month program along with a HLaC Participant Workbook (Table 3) used to support intervention delivery.

**Table 2 Tab2:** Healthy Living after Cancer intervention targets

Maintain a healthy body weight (BMI between 18.5 – 24.9 kg/m^2^)	
Engage in 30 minutes or more of moderate physical activity daily	
Consume a low saturated fat diet, including 5 serves of vegetables and 2 serves of fruit daily

**Table 3 Tab3:** Healthy Living after Cancer Participant Workbook content

Introduction to Healthy Living after Cancer (Section 1) • Importance of healthy living for cancer survivorship	
Plan for Success (Section 2) • Participant aims • SMART goal setting • Problem solving • Tracking your progress	
Physical Activity (Section 3) • Aerobic activity (e.g., brisk walking) • Flexibility/stretching • Strength training • Reducing sitting time	
Healthy Eating (Section 4) • Increasing serves of vegetables, fruit and wholegrains • Reducing fat (particularly saturated fat) intake • Eating the right amount of food (portion control) • Choosing the right types of food (low calorie, high nutrient)	
Weight Loss/Maintenance (Section 5) • Setting an appropriate weight loss goal (5 % – 10 % of initial body weight) • Strategies for achieving a 2000 kJ/day reduction	
Staying on Track (Section 6) • Positive thinking • Getting back on track after a slip • Planning ahead • Getting support from others • Celebrating success	

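### The activity and vegetable/fruit benchmarks in the economic appraisal label a reported level as improvement, with no baseline condition

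*Protocol article*

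**What the plan says.** The Economic appraisal section of the protocol article sets the frame: "outcomes will be defined using a series of pre-defined benchmarks based on pre-post program changes in the behavioural and anthropometric variables". It then gives three operational rules.

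- Activity: "For total physical activity, participants who reported achieving 150 minutes/week are considered as having made improvements in their physical activity level".
- Diet: "participants who reported achieving the target of 5 and 2 serves/day, respectively, are classified as having made positive changes in their dietary behaviour".
- Weight, only where weight loss is indicated: success goes to "those who recorded a body weight reduction at follow-up ≥3 % of their baseline weight".

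The benchmarks are then used as outcomes: "Regression analysis will be used to assess the relationship between completion of stages and outcomes achieved". The section hypothesises better outcomes in Stage 3 completers than in Stage 2 completers, and better in Stage 2 than in those who stop at Stage 1. A sensitivity analysis will "explore the impact of varying assumptions about the cut-offs used to define improvements in the secondary outcomes".

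Two other places bear on the point. The criteria under Screening and consent ask that participants want help with healthy living; they do not ask that participants be below any activity or dietary target. The Background says of cancer survivors in general that "over 50 % do not meet physical activity recommendations, and 90 % do not meet dietary guidelines".

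**The concern.** The frame is change, but two of the three rules are levels. The words that attach a label to the level (improvement, positive change) claim something that the rule does not test. The weight rule in the same paragraph is measured against the participant's own baseline, so the three benchmarks are not on one footing.

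Two uses are at stake. The first is the number of participants said to have improved, which is part of the evidence meant to inform decisions on sustained funding. The second is the stage regression. If the share already at target on entry differs between early leavers and full completers, a stage gradient can appear, or be hidden, for reasons unrelated to change during the program. The design has a single group, so a participant's baseline is the only reference against which change can be judged.

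**Working it through.** **1. The plan's own figure.** There is none to reproduce. The document gives no expected success proportion for any benchmark and no share of enrolees at target on entry. Its power statement concerns mean changes in the secondary outcomes and does not bear on this point.

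**2. The activity rule applied to single cases** (illustrative values, min/week).

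| Baseline | Follow-up | Labelled improved? | Actual change |
|---|---|---|---|
| 200 | 200 | yes | none |
| 300 | 160 | yes | decline of 140 |
| 0 | 140 | no | rise of 140 |

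**3. Whether anything else in the document repairs it.** Eligibility does not exclude people at target. The sensitivity analysis moves the threshold, and anyone above the new threshold at both times still counts as improved.

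**4. Zero-change check.** Enrolment of 900 with 30 % attrition gives 900 × 0.70 = 630 completers. If nobody changed, the rule would label every baseline achiever a success: 63 of 630 if 10 % start at target, 189 if 30 % and 252 if 40 %. A rule requiring a move from below target to at or above it gives 0.

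**5. With some change.** Let p0 be the share at target at baseline, r the share of those still at target at follow-up, and c the share of the rest who newly reach it.

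- Labelled improved = p0·r + (1 − p0)·c
- True crossings = (1 − p0)·c

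Assumptions, none of them from the document: r = 0.90; c = 0.20 or 0.30; p0 = 0.10, 0.30 or 0.40. Shares are of all completers.

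| p0 | c | Labelled | True crossings | Ratio |
|---|---|---|---|---|
| 0.10 | 0.20 | 0.09 + 0.18 = 0.27 | 0.18 | 1.5 |
| 0.10 | 0.30 | 0.09 + 0.27 = 0.36 | 0.27 | 1.3 |
| 0.30 | 0.20 | 0.27 + 0.14 = 0.41 | 0.14 | 2.9 |
| 0.30 | 0.30 | 0.27 + 0.21 = 0.48 | 0.21 | 2.3 |
| 0.40 | 0.20 | 0.36 + 0.12 = 0.48 | 0.12 | 4.0 |
| 0.40 | 0.30 | 0.36 + 0.18 = 0.54 | 0.18 | 3.0 |

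**6. The stage regression.** Take the same r = 0.90 and c = 0.30 in every stage, but suppose that 30 % of Stage 1 and 50 % of Stage 3 participants start at target.

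- Stage 1: 0.30 × 0.90 + 0.70 × 0.30 = 0.48
- Stage 3: 0.50 × 0.90 + 0.50 × 0.30 = 0.60
- Odds ratio: (0.60/0.40) / (0.48/0.52) ≈ 1.6

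The hypothesised gradient appears although conversion is identical. If instead p0 and r are equal across stages, the difference in labelled success is (1 − p0) times the difference in c, so a real stage effect is diluted. The distortion can go either way.

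**The case against.** The best defence is that the opening sentence governs the rest: benchmarks based on pre-post change, together with the verb for achieving a level, could mean moving up to that level during the program, condensed for a journal article. That reading cannot be excluded. But neither rule states it, and the weight rule shows that a baseline reference was written where one was intended. At the least, the frame and the rules have to be reconciled.

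It is also fair to say that activity often declines after cancer treatment, as the Background notes, so staying at target may be a benefit. That argues for reporting maintenance under its own name, not for calling it improvement. Adjustment of the stage regression for baseline status could sit in a fuller analysis plan, but it would not correct the count of improved participants.

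A reader might infer more than the document supports in three ways.

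- **That nearly half of enrolees already meet the activity target.** The Background says over 50 % of survivors in general fall short. It does not say by how much over, or against which minutes threshold, and people who seek support may be less active. For diet, the 90 % figure suggests a baseline share nearer 10 %, hence a smaller effect.
- **That cost per improved participant is understated by a known factor.** The section relates costs to completion and outcomes but specifies no such ratio.
- **That 150 min/week is wrong because Table 2 of the program section asks participants to "Engage in 30 minutes or more of moderate physical activity daily", which is 30 × 7 = 210 min/week.** An economic benchmark may sit below a program target, the section does not call 150 the target, and the planned variation of cut-offs can cover the difference.

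**Conclusion.** The point holds as a wrongly stated rule, not as missing detail. Followed literally, the activity and vegetable/fruit benchmarks count participants who stayed at target, or declined but remained above it, as improved. Under the assumptions in the working, the count exceeds true crossings by about 1.3- to 1.5-fold at a 10 % baseline share, 2.3- to 2.9-fold at 30 % and 3- to 4-fold at 40 %. Which of these applies cannot be settled from the document. That the stage regression mixes baseline status with change follows from the definition; the direction and size of the resulting bias depend on how baseline status varies by stage.

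The reach is limited to these benchmarks within the economic appraisal. The weight benchmark, the SF-12 and SF-6D differences and the mixed-model analyses of the secondary outcomes all use baseline and are sound on this point. The primary outcomes are service-level and descriptive. The wording should be corrected before analysis, but it does not threaten the study's main conclusions.

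**What to change.** Define success on each behavioural benchmark as below target at baseline and at or above target at follow-up, with participants below target at baseline as the denominator. Report those already at target separately, as maintained or lost. Use the same definition in the stage regression, and apply it at each cut-off in the sensitivity analysis.

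The cost is analysis wording only, because baseline values are already collected in the pre-program assessment. The downside is a smaller denominator and a less favourable proportion. With 630 completers and 30 % at target on entry, the denominator falls to 630 × 0.70 = 441, and the success proportion becomes 20-30 % (the assumed c) instead of 41-48 %.
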